### Technological device intervention

The project involves the testing of new technologies to support the patient and their caregiver, and the advice of a virtual information counter for technological aids and adapting to the home environment. The technologies to be employed are devices already widely used and marketed, are simple to use, and do not require significant technical expertise for installation and maintenance.

The technologies have been identified after a series of preliminary focus groups with caregivers and will include housing adaptations, such as luminous paths, home leaving sensors, sensors to detect night falls, gas and water leak sensors, and automatic lights. These devices will be assembled by an external contractor and linked to a single-board microcontroller, which will transmit alarm messages to the caregivers in case of need. The assembled devices will be assigned to subjects in the UP-TECH group after a joint evaluation of the home by the case manager and the engineer working in the virtual counter. Although these technologies can appear as low-tech in other industrialized countries, the degree of up-take of these devices in the houses of older Italians is almost non-existent.

Assistive technology will be installed by the case manager with the support of expert technicians who will also train the caregivers about their use (Figure 2).

**Figure 2 F2:**
[figure not shown]
The design of the UP-TECH kit.

### Nurse home visits and light support

All dyads participating in the UP-TECH group will receive three home visits by a specifically trained nurse. Home visits will occur at enrollment (M0), 6 months (M6) and 12 months (M12). Each visit will occur with the following steps: 1) telephone contact between the nurse and the family caregiver; 2) collection of informed consent (only at M0) and administration of the UP-TECH questionnaire; and 3) brief counseling/training of the caregiver regarding practical aspects of patient assistance, such as daily management of drug treatment, ergonomics of the home environment, stress management and care burden.

The creation of an information package for the 150 family caregivers included in the control group, illustrating the range of social and health services available in the local community, is planned. The information package will be delivered to the caregiver during home visits by the nurse. These caregivers and their families will continue to receive services in accordance with the usual care procedure, which, as already mentioned, does not include any other specific service from the health and social care systems. Some patients might receive additional care services, but this does not occur within the framework of an integrated case management program, and will depend on the presence of other pathological and social conditions.

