**Methods/design:**

A total of 450 dyads comprising AD patients and their caregivers in five health districts of the Marche region, Italy, will be randomized into three study arms. Participants in the first study arm will receive comprehensive care and support from a case manager (an *ad hoc* trained social worker) (UP group). Subjects in the second study arm will be similarly supported by a case manager, but in addition will receive a technological toolkit (UP-TECH group). Participants in the control arm will only receive brochures regarding available services. All subjects will be visited at home by a trained nurse who will assess them using a standardized questionnaire at enrollment (M0), 6 months (M6) and 12 months (M12). Follow-up telephone interviews are scheduled at 24 months (M24). The primary outcomes are: 1) caregiver burden, measured using the Caregiver Burden Inventory (CBI); and 2) the actual number of days spent at home during the study period, defined as the number of days free from institutionalizations, hospitalizations and stays in an observation unit of an emergency room.

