#### Outcomes of the study

The main outcomes of the study are: 1) caregiver burden, measured using the Caregiver Burden Inventory (CBI) multi-dimensional questionnaire, administered by a trained nurse. The CBI has five subscales: time-dependence burden, developmental burden, physical burden, social burden and emotional burden, and includes a set of 24 items evaluated using a 5-point Likert scale ranging from 0 (not at all) to 4 (very much), which are summed. A total score higher than 36 indicates a risk of stress, whereas scores near or slightly above 24 indicate a need to seek some form of respite care [36]. During the study, the Italian version of the CBI validated by Marvardi and colleagues will be used [37]; and 2) the actual number of days spent at home by the AD patient during the observation period, defined as days free from episodes of institutionalizations, inpatient hospitalizations and brief stays in an observation unit of an emergency room. This outcome will be treated as a continuous variable and will be calculated at each assessment (6 months, M6; 12 months, M12; and 24 months, M24) by subtracting from the total days of observation, the number of days of institutionalization in an assisted residence facility, care home and/or nursing home inpatient, hospitalizations, and brief stays in an observation unit of an emergency room.

In addition, the following outcomes will be evaluated at the end of the trial: 1) quality of life of the caregiver of the AD patient, measured using the Italian validated version of the quality of life questionnaire, SF-12 [38,39]; 2) anxiety and depression of caregivers, measured using the Italian validated version of the Hospital Anxiety and Depression Scale (HADS) [40,41]. HADS is a 14-item scale, seven of the items relate to anxiety and seven relate to depression, each item is a Likert scale scoring from 0 to 3, and this means that the overall score for either anxiety or depression will be between 0 and 21; and 3) abuse and mistreatment risk of AD patients, using the CASE instrument, an 8-item screening tool designed to assess caregivers for potential abuse. Answers are either given as ‘yes’ or ‘no’, and an answer of ‘yes’ for a question equals one point. A score of four or more is considered ‘abuse likely’, but a score of one can also mean that abuse is likely, depending on the question [42]. An Italian validation of this instrument is planned in a separate study at the end of the trial.

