#### Randomization, allocation and blinding

A letter with an invitation to participate in the project will be sent to a list of potential participants, randomly extracted from the AEU registers. A total of 640 invitations will be sent, considering a response rate of 70% (a reasonably high rate, since the project has been endorsed by the Italian regional health system and several local patients' organizations). Families agreeing to be contacted will receive a home visit by a nurse. Both caregivers and patients will be requested to sign a full informed consent to participate in the study. The nurses who will make the home visits and administer the questionnaires will be blinded at their first visit.

The allocation sequence will be generated using the statistical software STATA (College Station, TX, USA). Dyads in blocks of 15 and consequently enrolled will be sent by a nurse coordinator in the five health districts directly to the project manager (CC). In each block, five dyads will be allocated to each arm. The randomization will be performed by the project manager, who will not conduct any assessment related to treatment outcomes or have any contact with line staff involved in the intervention, in order to preserve allocation concealment and prevent selection bias (Figure 1).

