#### Assessments

All dyads will be interviewed using standardized tools. The interviewers will be the same nurses conducting the three home visits.

The first evaluation will also be the most in-depth. The UP-TECH ‘questionnaire 1’ is divided into three parts: the first focuses on AD patients (section A to C), the second part concerns caregivers (section D to H), while the final part measures the consumption of social and health care resources by the dyad (section I).

A nurse, trained to collect data, will administer a modified version of the interResident Assessment Instrument Contact Assessment (interRAI CA, Ann Arbor, MI, USA) to the AD patient, when possible, or to the caregiver, who will act as a proxy respondent [44]. The interRAI CA is a validated tool to support the decision-making process when managing the home and/or palliative care of the patient.

The instrument adapted from the interRAI CA will contain items designed to investigate the following areas: section A, general patient information: name, sex, date of birth, health district affiliation, housing conditions, surgery in the last 90 days and two main informal caregivers (questions about the benefits of the Italian legal system, Law 104/1992, were added); section B, screening information: the ability to make everyday decisions, ADLs, dyspnea, clinical status and perception of health status; and section C, clinical evaluation: changes in the ability to make everyday decisions, ability to understand other people, eyesight, reported indicators of depressed mood, behavioral problems, IADL difficulties, changes in ADL independence, disease diagnoses, falls, frequency of problems, pain, smoking, assessment of nutritional status, mode of eating, the highest stage of pressure ulcer, skin ulcer (not caused by pressure), other skin problems, traumatic injuries, treatments and services received, time since last hospitalization, and number of emergency room visits.

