## Discussion

The implementation of the UP-TECH project responds to the increasing need to cope with the consequences of the AD epidemic. It is in line with present policy and research priorities at both Italian and European levels [49,50].

Findings in this project are intended to support both health care and social service professionals and policy-makers in the enactment of future programs, addressing the increasing needs of AD patients and their caregivers. The rationale behind the project is that, despite the growing literature in this area, several controversies still need to be resolved and effective options need to be laid out in order to both avoid the institutionalization of AD patients and the burn-out of informal caregivers [11].

The project gathers the existing knowledge and related strategies in the area of dementia care, that is, the use of case management programs [8,15,16,26], new technologies [8,20,26], preventive home visits [51] and efforts toward integration of existing services [27-30], and tries to integrate them in an ambitious holistic design.

Possible limitations of the design should be mentioned. As the caregiver-patient dyads are allocated after the full consent, blinding is not required during the first home visit; however, blinding cannot be guaranteed during the second and third visits, or during the follow-up telephone call. Since the nurses will engage with patients and caregivers in long conversations, it is likely that they will be told about the social worker intervention or they will notice the technological toolkit installed in the home. In order to minimize the risk of performance and ascertainment bias, we will provide an *ad hoc* training course to nurse assessors, and we will keep as separated as possible the professionals intervening on the patients and caregivers (the social workers) from those assessing the outcomes (the nurses). In addition, we preserved the solidity of the study by choosing as one of the two primary outcomes, the number of days free from hospitalizations and other institutionalization episodes, a measure which is not likely to be influenced by an eventual un-blinding of the assessors.

Regarding the use of new technologies, the UP-TECH project does not entail the use of highly complex and innovative devices, but aims to test the effectiveness of simple marketed technological devices combined with case management and user-centered strategies.

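### The nurse who interviews for the CBI also delivers the control-only information package: a built-in, avoidable route to unblinding that the Discussion does not mention

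*Protocol article*

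**What the plan says.** Under Nurse home visits and light support, the protocol article plans the package for one arm only: "The creation of an information package for the 150 family caregivers included in the control group". On delivery it says: "The information package will be delivered to the caregiver during home visits by the nurse". The abstract describes the control condition in the same terms: "Participants in the control arm will only receive brochures regarding available services". Study design adds three nurse home visits in every arm. No section gives the package to the UP or UP-TECH arms.

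Assessments states: "The interviewers will be the same nurses conducting the three home visits". Outcomes of the study defines caregiver burden as "measured using the Caregiver Burden Inventory (CBI) multi-dimensional questionnaire, administered by a trained nurse".

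On blinding, Randomization, allocation and blinding states: "The nurses who will make the home visits and administer the questionnaires will be blinded at their first visit". The Discussion accepts that blinding cannot be assured at the second and third visits or at the follow-up call. It gives two reasons: nurses may hear about the social worker, or may see the installed kit. Its mitigations include assessor training and this: "we will keep as separated as possible the professionals intervening on the patients and caregivers (the social workers) from those assessing the outcomes (the nurses)".

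**The concern.** A nurse who has to bring a package that only control families receive must know which families are controls. That nurse also conducts the CBI interview. The protocol therefore passes the allocation to the assessor as part of the planned procedure, whereas the Discussion presents unblinding as something that happens incidentally during long conversations or in a home with sensors.

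At stake is the CBI comparison. The CBI is subjective and collected by interview, so an interviewer who knows the arm can influence answers through tone, prompting or clarification. The other primary outcome, days at home, is less exposed, because hospital and residential episodes are also retrieved from regional databases (Integration of collected data with Alzheimer Evaluation Units). The Discussion itself relies on that outcome as the one robust to unblinding, which leaves the CBI as the vulnerable one.

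**Working it through.** This is a question of procedure. The protocol states no figure to reproduce, so the sections are set side by side.

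1. **Does the package identify the arm?** Yes. It is prepared for the 150 control caregivers (Nurse home visits and light support). The abstract and Study design make it the only component specific to that arm.
2. **Who delivers it?** The nurse, at home visits (same section).
3. **Who collects the CBI?** The same nurses (Assessments; Outcomes of the study).
4. **When does the arm exist?** Consent is collected at M0 (Nurse home visits and light support). Allocation comes after full consent (Discussion), in blocks of 15 sent to the project manager (Randomization, allocation and blinding).
5. **Which visits are possible?** Nurse home visits are at M0, M6 and M12 only.
   - *M0:* the nurse would have to know the arm at a visit where she is stated to be blinded and where allocation has not yet happened.
   - *M6:* a nurse who carries the package knows the arm before the M6 interview. Even if she learned it only after the questionnaire, she would know it at M12.
   - *M12:* a nurse who carries the package knows the arm before the M12 interview.
6. **Does the Discussion cover this?** No. Both causes it names reveal intervention dyads. The delivery task reveals control dyads and is assigned by the protocol.

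**How many dyads.** 150 controls as randomized. With the planned 15% drop-out, 150 × 0.85 = 127.5, so about 127 are still followed.

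**What a bias would mean, by assumption only.** The document gives no bias size. Suppose interviewing produced a spurious difference of 1 or 2 CBI points between two arms.
- Against the planned effect in Sample size calculation, 32.5 − 24 = 8.5 points, this is 1/8.5 = 12% or 2/8.5 = 24%.
- With 127 per arm and a common SD s, the standard error is s × √(2/127): 2.26 for s = 18 and 1.51 for s = 12, the two SDs the protocol gives.
- With no true effect, the two-sided 5% false-positive rate is Φ(−1.96 + b/SE) + Φ(−1.96 − b/SE), where b is the spurious difference:

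| b (points) | SD 18 | SD 12 |
|---|---|---|
| 0 | 5% | 5% |
| 1 | 7% | 10% |
| 2 | 14% | 26% |

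These rates describe any spurious difference of that size, whatever its source. They do not estimate what package delivery adds.

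**The case against.** The strongest reply is that the protocol never claims masked assessment after baseline. It limits stated blinding to the first visit, says openly that later visits may not be blind, and offers mitigations. If nurses are likely to recognise the two intervention arms from conversation or equipment, many controls become identifiable by absence. This stands: the increment from the delivery task is smaller than the whole control arm suggests. It does not remove the point, because a conceded residual risk differs from an assigned task that makes the knowledge certain and could easily be dropped.

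Three stronger readings are tempting, and the document does not support them.

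- *A reader might infer that the protocol flatly contradicts its promise of separation.* The promise is qualified and names the social workers as the intervening staff. Nurse delivery fits poorly with its purpose but does not breach its wording.
- *A reader might infer that an unblinded nurse scores the CBI.* The caregiver answers the items, which are summed; the nurse administers them. The caregiver also knows what support has been received, so respondent bias exists whoever brings the package. The nurse can add bias only through the interview.
- *A reader might infer that controls get their package six months late.* The delivery visit is not stated, nor whether handover precedes or follows the questionnaire. A condensed article may leave that detail to the full protocol. Nor does the point depend on it: each of the three visits leads to one of the two problems, a breach of M0 blinding or an assessor who knows the control dyads.

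**Conclusion.** The point holds in limited form. The protocol gives the CBI interviewer an arm-specific delivery task. Given allocation after M0 consent, that task either conflicts with the stated blinding at M0 or tells the assessor which dyads are controls by M6 or M12. The Discussion's account of unblinding leaves this route out.

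It applies to every control dyad still visited, but its net effect beyond the conceded unblinding is unknown. Neither the size nor the direction of any bias can be derived from the document; the percentages above rest on assumed shifts. The conclusion assumes that the package goes to controls only and that nurses make no home visits beyond the three described, as the text states. This is a cheap improvement to the conduct of the trial. It does not invalidate the design.

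**What to change.** - Take delivery away from the assessing nurses. The coordinating centre, or other staff who assess no outcomes, posts the package to control families once their block has been allocated.
- State that the assessing nurses are not told the allocation.
- Reconcile Randomization, allocation and blinding, Nurse home visits and light support, and the Discussion, so that delivery, timing and the account of unblinding agree.
- Optionally, have the nurse record a guess of the allocation after the questionnaire at M6 and M12, so that the remaining unblinding can be reported.

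The cost is postage for 150 packages and, if adopted, one extra item on the nurse's form. There are two downsides: mail replaces personal handover, which slightly changes how the control condition is delivered, and incidental unblinding through conversation or visible equipment remains.

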#### Assessments

All dyads will be interviewed using standardized tools. The interviewers will be the same nurses conducting the three home visits.

The first evaluation will also be the most in-depth. The UP-TECH ‘questionnaire 1’ is divided into three parts: the first focuses on AD patients (section A to C), the second part concerns caregivers (section D to H), while the final part measures the consumption of social and health care resources by the dyad (section I).

A nurse, trained to collect data, will administer a modified version of the interResident Assessment Instrument Contact Assessment (interRAI CA, Ann Arbor, MI, USA) to the AD patient, when possible, or to the caregiver, who will act as a proxy respondent [44]. The interRAI CA is a validated tool to support the decision-making process when managing the home and/or palliative care of the patient.

The instrument adapted from the interRAI CA will contain items designed to investigate the following areas: section A, general patient information: name, sex, date of birth, health district affiliation, housing conditions, surgery in the last 90 days and two main informal caregivers (questions about the benefits of the Italian legal system, Law 104/1992, were added); section B, screening information: the ability to make everyday decisions, ADLs, dyspnea, clinical status and perception of health status; and section C, clinical evaluation: changes in the ability to make everyday decisions, ability to understand other people, eyesight, reported indicators of depressed mood, behavioral problems, IADL difficulties, changes in ADL independence, disease diagnoses, falls, frequency of problems, pain, smoking, assessment of nutritional status, mode of eating, the highest stage of pressure ulcer, skin ulcer (not caused by pressure), other skin problems, traumatic injuries, treatments and services received, time since last hospitalization, and number of emergency room visits.

The family caregiver will be given a questionnaire consisting of five sections: section D, demographic and socio-economic status: age, sex, housing, income and social network support using the Multidimensional Scale of Perceived Social Support (MSPSS) [45]; section E, lifestyle: information regarding diet, smoking and alcohol consumption; section F, clinical evaluation: information on the perception of caregiver depression and anxiety (HADS) [40], the perception of well-being of the caregiver (quality of life questionnaire, SF-12) [38], and the presence of chronic diseases; section G. anthropometric measurements, including control of blood pressure and measurement of body mass index (BMI), via evaluation of height and weight; and section H, the caregiving relationship: caregiver burden measured with the CBI [36] and the risk of domestic abuse in the caregiving relationship [42].

In the last section of the questionnaire (section I, consumption of resources by the AD patient), the family caregiver will be asked for information regarding: resource consumption of the AD patient (for example drug therapy, visits to general practitioners and specialists, use of home nursing, and hospitalizations); use of treatment/care (for example nurse and formal caregiver) paid for by the patient/caregiver dyad, expressed in number of hours per week of treatment (or care); and the number of hours of work lost by the caregiver (hours per week) to provide assistance for the AD patient (productivity loss).

After the start of the study, at 6 months (M6) and 12 months (M12), respectively, a second and a third assessment will be conducted. Twelve months after the end of the trial (M24), follow-up telephone calls will be made to study participants in order to assess the impact of the interventions over the medium term.

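### The Caregiver Burden Inventory, a subjective primary outcome, is administered by nurses whom the protocol expects to be unblinded at 6 and 12 months; sealed written self-completion before the interview would take them out of asking and scoring it

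*Protocol article*

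**What the plan says.** **Outcome and assessor.** Under Outcomes of the study, the CBI is a primary outcome: 24 items scored 0 to 4 and summed, "administered by a trained nurse". The Assessments section has the same nurses interview at all three home visits.

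**Questionnaire order.** Assessments describes one form, questionnaire 1, used at the first evaluation: "The first evaluation will also be the most in-depth". Sections A to C concern the patient. Then "the second part concerns caregivers (section D to H), while the final part measures the consumption of social and health care resources by the dyad". The last items in section C are "treatments and services received, time since last hospitalization, and number of emergency room visits". The CBI comes later: "section H, the caregiving relationship: caregiver burden measured with the CBI [36"]. The detailed resource questions follow it: "In the last section of the questionnaire (section I, consumption of resources by the AD patient"). For M6 and M12 the article says only that a second and a third assessment take place. It does not give their content or order.

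**Blinding.** Randomization, allocation and blinding has the nurses blinded at the first visit. The Discussion says that blinding cannot be assured at the second and third visits, because conversations are long and "it is likely that they will be told about the social worker intervention", or because they will notice the installed kit. Its answers are training of the nurse assessors, keeping intervention staff and assessors apart as far as possible, and a second primary outcome that it regards as less open to this bias.

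**The concern.** The CBI consists of graded judgements about strain. Wording, prompting and the coding of a hesitant answer can all move the score, and the person doing these things at M6 and M12 is expected to know the arm. A systematic lean of this kind does not shrink as the sample grows. The protocol acknowledges the risk, but its safeguards leave the nurse as both asker and scorer. The second primary outcome protects the trial's other conclusion and does nothing for the CBI result.

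The one documented section order adds to the concern. It puts the CBI late in the interview, after an item on services received that could prompt mention of the case manager.

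**Working it through.** The point rests on reading the sections together. The arithmetic only shows what a bias of a given size would do.

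**1. Who scores, and what they know.** Outcomes of the study has a nurse administer the CBI. Assessments has the same nurses return. The Discussion expects them to learn the arm at M6 and M12. Taken together, an assessor who is expected to be unblinded collects a subjective primary outcome.

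**2. What the safeguards reach.** Training may reduce a lean but leaves the nurse in place. Staff separation does not prevent disclosure by the caregiver or sight of the kit. The second primary outcome is a different endpoint.

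**3. What the order shows.** In questionnaire 1 the sequence is A to C (patient, with the services item in C), D to G (caregiver), H (CBI), I (resource use). That form is used at M0, before allocation, when there is no arm to disclose. Whether M6 and M12 keep the order is not stated.

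**4. Illustration of size.** Inputs from Sample size calculation: SD 18 in control and 12 in treatment, means 32.5 and 24, drop-out 15%, and 150 caregivers read as per arm. Sidedness is not stated for the CBI; two-sided 5% is assumed.

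- Evaluable per arm: 150 × 0.85 = 127.5.
- Standard error of the difference: √(18²/127.5 + 12²/127.5) = √(468/127.5) = 1.916. With SD 18 in both arms: √(648/127.5) = 2.254.
- Assumed lean: 0.05 to 0.10 of a scale step per item. Over 24 items: 24 × 0.05 = 1.2 points; 24 × 0.10 = 2.4 points.
- False-positive rate with no true effect: P(|Z + bias/SE| > 1.96).

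| Assumed bias | SDs 18 and 12 | SD 18 in both |
|---|---|---|
| 1.2 points | 9.6% | 8.3% |
| 2.4 points | 24.0% | 18.7% |

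The design difference is 32.5 − 24 = 8.5 points, so these leans are 1.2/8.5 = 14% and 2.4/8.5 = 28% of it. The documents give no size for the bias, and no way to split it between nurse and caregiver.

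**The case against.** The strongest case on the other side is that the Discussion already discloses the limitation and responds to it, that nothing is misstated, and that the layout of follow-up forms is detail an article may leave to the full protocol. All of this is fair. It makes the point a design improvement and not an error. It does not answer the fact that the article fixes nurse administration of the CBI while expecting the nurse to be unblinded.

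A reader might infer more than the documents support:

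- *That the nurse usually knows the arm before scoring.* The Discussion calls disclosure likely but does not say when in the visit it happens. The A-to-I order is documented only for M0, and the most detailed resource questions already follow the CBI.
- *That asking the CBI first would be enough.* The kit is visible, the nurse delivers the control group's information package, a telephone contact precedes each questionnaire, and what is learned at M6 carries to M12. Reordering alone would help mainly the UP versus control comparison at M6.
- *That the mode is contradictory*, because Assessments says "The family caregiver will be given a questionnaire consisting of five sections". The same caregiver questionnaire includes blood pressure, height and weight, and the other sections consistently have nurses administer the questionnaires. The mode is nurse administration throughout.
- *That the M24 telephone call has the same problem.* The article does not say that the CBI is collected at M24; Outcomes of the study names M24 only for days at home.

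It is also true that the respondent knows what support is being received, so response bias survives any change of mode.

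**Conclusion.** The point holds in a limited form. A subjective primary outcome is asked and scored at M6 and M12 by nurses whom the protocol itself expects to be unblinded, and the stated mitigations do not remove their influence on it. The late position of the CBI adds to this only if the M0 order is reused, which is an inference.

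The rates of about 8% to 24% depend on an assumed bias of 1.2 to 2.4 points, the protocol's SDs and drop-out, 150 per arm and a two-sided test. They show that a small lean would matter. A reader might take them as the inflation present in this trial or as the gain from the fix, but the documents support neither, and the share of bias that the fix removes cannot be computed from them. The case for the change is that it is cheap and acts on the nurse's part of the problem whether or not she knows the arm.

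**What to change.** At M0, M6 and M12, in the same mode in all three arms, have the caregiver complete the CBI in writing as the first step of the visit and seal it before the interview and the counseling begin. The nurse reads the items aloud only when the caregiver cannot complete the form, and each such case is recorded. Including M0 keeps baseline and follow-up scores in one mode. Change Outcomes of the study, which now specifies nurse administration, and take the CBI out of the interview sequence in Assessments. The documents do not say whether the cited Italian version has been used in self-completed form, so the sponsor should confirm this first.

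The cost is a paper form and a reordered questionnaire, with no extra staff foreseen. The downsides are some more blank items and a recorded minority assessed in a second mode. The change reduces nurse-related ascertainment bias only, so the Discussion should continue to state that caregivers know what support they receive.
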